#### **Inclusion Criteria**

1. Patients with an stable serum creatinine < 3.0 mg/dl
2. Patients have to be on an immunosuppressive regimen with  $\geq 720$  mg/d Myfortic® and Sandimmun® Optoral
3. Patients with a proteinuria < 500 mg/g creatinine

#### **Exclusion Criteria**

Of all patients included into the study at BL1 (prior to transplantation), those can not continue into the randomized study period, in whom one of the following criteria are met at BL2, prior to randomization:

1. Graft loss after current transplantation (since Baseline visit 1)
2. Patients who received a depleting antibody therapy or more than 10mg/day prednisolon (or an equivalent oral steroid therapy)
3. Patients who suffered from rejection (more than BANFF 1A), recurrent acute rejection, or steroid resistant acute rejection
4. Patients with thrombocytopenia (platelets < 75,000/mm^3), with an absolute neutrophil count of < 1,500/mm^3 or leucopenia (leucocytes < 2,500/mm^3), or hemoglobin < 6 g/dL
5. Evidence of severe liver disease (incl. abnormal liver enzyme profile, i.e. AST, ALT or total bilirubin > 3 times ULN)
6. Current dialysis dependency at Baseline visit 2
7. Patients with clinically significant infection requiring continued therapy which would interfere with the objectives of the study
8. Presence of intractable immunosuppressant complications or side effects (e.g., severe gastrointestinal adverse events) at randomization visit (Baseline visit 2)

## 6 Treatment

### 6.1 Components of Investigational therapies

#### Investigational drug

- **Certican®**  
Active ingredient: Everolimus (RAD001)  
Galenic form: Tablets  
Dose: one tablet containing 0.5 mg, 0.75 mg or 1.0 mg  
Dosing schedule: initially 3 mg on day 1 and 2 x 1.5 mg on day 2 after randomization afterwards based on blood trough level (5 – 10 ng/mL)  
Packaging: Blisters of 10 Tablets
  
- **Simulect®**  
Active ingredient: Basiliximab  
Galenic form: lyophilisate in vials with ampoules of sterile water for injection (5 mL)  
Dose: one vial containing 20 mg lyophilisate  
Dosing schedule: 2 x 20 mg (day 0 (2 hrs prior to Tx) and day 4 post Tx) in Control and Certican group. Additional doses of Simulect (each 20 mg) on Week 7 and 12 in Certican group to be applied as i.v. bolus injection  
Packaging: packages of 1 lyophilisate in vial with ampoules of sterile water

#### Other immunosuppressive drugs

- **Sandimmun® Optoral**  
Active ingredient: Cyclosporine A  
Galenic form: capsules  
Dose: one capsule containing 10, 25, 50, or 100 mg  
Dosing schedule: according to blood level  
Packaging: trade ware will be used
  
- **Myfortic®**  
Active ingredient: Enteric Coated Mycophenolate Sodium (EC-MPS)  
Galenic form: Tablets  
Dose: one tablet containing 180 mg or 360 mg  
Dosing schedule: “loading dose” regimen: week 1 – 2: 2880 mg/day; week 3 – 6: 2160 mg/day; week 7 – 24: 1440 mg/day, if tolerated

Packaging:                      dose reduction due to side effects are possible  
                                         trade ware will be used

- **Corticosteroids**

according to local standard. Steroid withdrawal after week 2.

## **6.2 Treatment groups**

At Baseline visit 2 (Visit 3, Week 7) patients will be assigned to one of the following two treatment groups in a 2:1 ratio:

**Group 1: Certican:** switch to immunosuppressive regimen consisting of:  
Certican® + Myfortic®

**Group 2: Control:** maintain prior immunosuppressive regimen consisting of:  
Sandimmun® Optoral + Myfortic®

## **6.3 Treatment assignment**

A randomization list will be produced by or under the responsibility of Novartis Biometrics Department using a validated system that automates the random assignment of treatment groups to randomization numbers in the specified 2:1 ratio (Certican®, Control). Two sets of randomization numbers will be prepared for stratified randomization, one set for the group of patients who did not experience any rejection between Baseline 1 and Baseline 2 (Visit 3/Week 7) and one set for the group of patients who did experience at least one rejection in this period. Randomization numbers will be different in the two sets. The randomization scheme will be reviewed and locked after approval. According to the recommendations given in the ICH E9 Guideline "Statistical Principles for Clinical Trials" (CPMP, 1998), the used block length is specified in a separate document which is withheld from the study centers. The randomization list will be kept sealed in a secure location.

At Baseline 1 which has to be performed prior to the transplantation surgery, patients will be assigned a unique patient identification by the investigator. The patient identification has two parts. The first part is the four-digit center number, which is assigned by Novartis. The second part will be assigned by the investigator starting with number "00001" in each study site. Once assigned to a patient, the patient identification will not be reused. If the patient fails to be randomized for any reason, the patient's identification and the reason for not being randomized will be entered on

the Study Completion Page. Note: The patient identification is different from the randomization number.

At Baseline 2 (visit 3, Week 7), all eligible patients will be given a randomization number that assigns them to one of the treatment groups. The randomization numbers are sequentially allocated to the patients per center in the order of inclusion in the randomized treatment period. Each patient will receive only that treatment regimen which is labeled with the randomization number allocated to him/her.

Randomization of individual patients will be performed centrally by the designated CRO. Allocation of a patient to one of the two treatment groups will be performed in the following steps.

1. Information about patient inclusion (BL 1)  
Study sites will inform the randomization department of the designated CRO about each patient inclusion via fax
2. Reminder (Visit 2/Week 2):  
By a reminder that will be included in the CRF of the Week 2 assessments, site will be reminded to schedule the next Visit 3 (Week 7) on time
3. Randomization (BL 2):  
At day of randomization, the site will provide the patient information of eligible patients to the designated CRO by fax.  
Depending on the stratum (previous rejections yes/no), the designated CRO randomization department will allocate the patient the next free consecutive randomization number allocated to the site per stratum. Randomization number and allocated treatment (according to the randomization list) will be provided to the site by fax.

The randomization number will be entered on the CRF of an individual patient.

## **6.4 Treatment blinding**

Not applicable. This is an open-label study.

## **6.5 Treating the patient**

### **6.5.1 Study drug administration**

Each study site will be supplied by Novartis with study drug (everolimus, Certican®) for patients who are treated in the Certican®-group. Study drug will be provided as tablets, packaged in boxes containing strips of blisters packed tablets, and labeled as RAD001 Tablets. Study drug will be available in 0.75 mg strength. Additional medication for dose titrations will be provided in 0.5 mg and 1.0 mg strength.

One component of the box consists of a 2-part label which includes an identifier of each single box of study medication. Before dispensing the study medication to an

individual patient, investigator staff must enter the 4-digit patient code and the date of dispensing of the medication box on both parts of the label. The outer part of the label will be detached from the packaging and affixed to the source document (Drug Label Form in the CRF) containing that patient's unique patient number.

For the other immunosuppressive drugs (Simulect® induction therapy, Sandimmun® Optoral, Myfortic®, Corticosteroids) the patient will receive a prescription.

Patients randomized to Certican®-group will receive additional doses of Simulect® (each 20 mg) on Week 7 and 12 as rejection prophylaxis. These doses will be provided as investigational drug.

The prescribed total daily dosage of the immunosuppressive drugs should be divided in two (equal) doses, applied 12 hours apart (i.e. 08:00 a.m. and 08:00 p.m.).

The investigator should instruct the patient to take the study drug exactly as prescribed in order to promote compliance. All dosages prescribed and dispensed to the patient and all dose changes during the study must be recorded on the Dosage Administration Record CRF.

In patients randomized to the Certican® regimen, withdrawal of Sandimmun® Optoral and commencement of Certican® will be performed in different steps as described below, starting at Visit 3 (Week 7).

- Step 1: Day 1 morning: Myfortic® + Sandimmun® Optoral  
Day 1 evening: Myfortic® + Sandimmun® Optoral + Certican® (3 mg)
- Step 2: Day 2 morning: Myfortic® + Certican® (1.5 mg)  
Day 2 evening: Myfortic® + Certican® (1.5 mg)
- Step 3: Day 3 morning: Myfortic® + Certican® (TL 5 – 10 ng/mL)

Dose increase / adjustment of Certican® and Sandimmun® Optoral should be performed based on the investigator's experience and the given therapeutic blood levels, adverse events, etc. Dose adjustments should be monitored 7 days  $\pm$  2 later (Visit 4).

Sandimmun® Optoral will be administered according to blood trough levels: week 1 – 4 150 – 200 ng/ml (all patients), week 5 – 6: 100 – 150 ng/ml (all patients), week 7 – 18: 100 – 150 ng/ml (only patients in Control group), week 18 – 24: 80 – 120 ng/ml (only patients in Control group).

Myfortic® will be given in both groups according to the "loading dose" regimen: week 1 – 2: 2880 mg/day; week 3 – 6: 2160 mg/day; week 7 – 24: 1440 mg/day.

Corticosteroids will be added to the immunosuppressive regimen according to local standard but with minimum dose of 5 mg/day. Steroids will be withdrawn after week 2 in both groups.

### 6.5.2 Permitted study drug adjustments

For patients who are unable to tolerate the protocol-specified dosing schedule, dose adjustments are permitted in order to keep the patient on study drug. The recommendations described below should be followed as far as clinically feasible.

#### **Certican®**

Because Certican® is the mainstay of immunosuppression in the CNI-free group, Certican® dose should be continued on a stable level according to trough levels. Therefore reduction or elimination of Myfortic® should be considered first (step 1) before adjusting the Certican® dose (step 2).

Steroids could be added to the immunosuppressive regimen if necessary (step 3). In case of not achieving sufficient immunosuppression Sandimmun® Optoral could be added to the IS treatment in the Certican®-group (step 4).

Target therapeutic ranges for Certican® (everolimus) whole blood trough levels after CNI-removal should be 5 to 10 ng/mL.

Dose adjustments may be performed if Certican® (everolimus) whole blood trough levels outside the target range are measured. Dose adjustments of Certican® should be monitored 7 days later by a measurement of the everolimus blood trough level.

In both renal and heart transplantation, everolimus trough concentrations  $\leq 3$  ng/mL were associated with a significantly lower protection from acute rejection compared with trough levels  $> 3$  ng/mL. Although hyperlipidemias were common over the full exposure range, they responded to corticosteroid dose reduction, dietary management, and lipid-lowering therapies, and were, therefore, not dose-limiting. The incidence of leukocytopenia did not show any exposure-response relationship to everolimus trough concentrations. The incidence of notable thrombocytopenia ( $< 100 \times 10^9/L$ ) increased with Certican® exposure; however, the incidence of clinically meaningful platelet reductions ( $< 75 \times 10^9/L$ ) was generally low.

When Certican® is used with conventionally dosed CsA, the lower therapeutic concentration was 3 ng/mL (Kovarik et al., 2001, 2002b; Vitko et al., 2004). For safety reasons, therefore, a higher lower limit seems necessary, when CsA is discontinued. This was the rationale to increase the lower limit to 5 ng/mL after withdrawal of Sandimmun® Optoral. A more precise upper therapeutic limit could not be defined. There is, however, limited clinical experience that doses causing concentrations  $> 8$  ng/mL may lead to an increased frequency of side effects (Kovarik et al., 2001, 2002b, 2002c; Vitko et al., 2004). Certican® (everolimus) trough levels  $> 12$  ng/mL should be avoided.

If Certican® medication is interrupted for safety related considerations for more than 14 consecutive days within the 6 months study treatment (or cumulative for more than 4 weeks), discontinuation of the medication should be considered and the patient should be withdrawn from the study. Appropriate information needs to be recorded on the Dosage Administration CRF.

### **Sandimmun® Optoral**

Target therapeutic range for cyclosporine whole blood levels should be the following.

| Group      | Certican            | Control |
|-------------------|----------------------------|----------------|
| Timepoint  | C0-h levels [ng/ml] |                |
| Week 1 – Week 4   | 150 – 200                  | 150 – 200      |
| Week 5 – Week 6   | 100 – 150                  | 100 – 150      |
| Week 7 – Week 18  | 0                          | 100 – 150      |
| Week 18 – Week 24 | 0                          | 80 – 120       |

Dose may be adjusted if measured cyclosporine whole blood levels are outside the target range. In case of severe CsA toxicity, dose reductions below the target levels may be performed on the investigators' discretion.

If Sandimmun® Optoral medication is interrupted for more than 14 consecutive days within the 6 weeks (Certican group), respectively 6 months (Control group) of study treatment (or cumulative for more than 4 weeks), discontinuation of the medication should be considered and the patient should be withdrawn from the study.

In the CNI-free group the Sandimmun® Optoral dosage will be reduced starting at Week 7 and removed completely the day after.

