| Rejection episodes                           | ← as necessary → |   |                      |                |    |    |                  |
| Renal biopsy                                 | ← as necessary → |   |                      |                |    |    |                  |
| Infections                                   | ← as necessary → |   |                      |                |    |    |                  |
| Tumour                                       | ← as necessary → |   |                      |                |    |    |                  |
| AEs                                          | ← as necessary → |   |                      |                |    |    |                  |
| SAEs                                         | ← as necessary → |   |                      |                |    |    |                  |
| Comments                                     | ← as necessary → |   |                      |                |    |    |                  |
| Concomitant therapy                          | ← as necessary → |   |                      |                |    |    |                  |
| Immunosuppressive therapy                    | ← as necessary → |   |                      |                |    |    |                  |
| End of treatment / End of study  |                  |   |                      |                |    |    | x                |

BL: Baseline visit 1: prior to transplantation  
EOS: End of Study

BL2: Baseline visit 2 : day of randomization

- 1) Visit 1 (BL ) is to be performed prior to transplantation
- 2) At end of study (Week 24 post Tx) or at the time of early discontinuation
- 3) Blood level control on Day 7 ± 2 after randomization
- 4) Optional
- 5) To be assessed only if Sandimmun® Optoral or Certican® are administered at that visit. Certican®-troughlevels will be determined locally.
- 6) Optional – if part of center standard procedure – control biopsies may be taken only at indicated time points

Patients should be seen for all visits on the designated day or as close to it as possible. Visit 3 (Week 7 – BL2) may be performed within a time window of week 7 and week 8.

### Visit 1 (day 0 / Week 0) – Baseline visit 1

The Baseline visit 1 assessment is to be performed prior to transplantation, i.e. within 24 hours before surgery.

1. Patient signs informed consent
2. Patient's eligibility for the study according to in- and exclusion criteria will be checked

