### **Visit 3 (Week 7 post Tx) – Baseline visit 2**

This visit may be performed within a time window of week 7 and week 8.

1. Patient's eligibility for the study according to in- and exclusion criteria will be checked
2. The patient will be randomized to one of the two treatment arms taking stratification into account (occurrence of rejection between BL1 and BL2).  
Study medication for the following treatment weeks will be handed over to the patient; amount and mode of administration will be explained to the patient
3. A complete physical examination will be performed.
4. (Changes in) smoking status will be recorded and the cardiovascular risk (Framingham Score, see [Appendix 7](#)) will be calculated.
5. Vital signs will be measured.

6. Venous blood will be drawn for measurement of hematology and biochemistry (complete program)
7. An oral glucose tolerance test (OGTT) with a concomitant insulin measurement will be performed.
8. Venous blood will be drawn for measurement of viral serology
9. Venous blood will be drawn for measurement of the C0-h level of cyclosporine
10. Urinalysis will be performed, the Glomerular Filtration Rate (GFR) will be assessed.
11. Changes in Concomitant medications / significant non-drug therapies will be recorded
12. (Changes in) immunosuppressive medication will be recorded
13. Information on rejection episodes, renal biopsies, hospitalization, infections, and other (S)AEs that occurred since the last visit will be recorded.
14. Optionally – if part of center standard procedure – a control biopsy may be taken. Control biopsies should be assessed by a central nephropathologist and should only prompt therapy in cases of severe rejection, infection or toxicity. In order to avoid any bias, which could interfere with the objectives of the study, investigators should be kept blinded until completion of the study.

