## **7.9 Pharmacokinetics**

The actual sample collection times, and the date and time of the previous drug dose (Certican® or Sandimmun® Optoral) will be recorded on CRF using a 24 hour clock.

Cyclosporine whole blood levels will be measured starting at Visit 2. For patients of the Control group cyclosporine blood level will be measured at every study visit, for patients of the CNI-free Certican group cyclosporine blood level will be measured until Sandimmun® Optoral is removed from the immunosuppressive regimen (Visit 3, Week 7).

Certican® (everolimus) blood levels will be measured in patients of the Certican® group starting 7 days after first Certican® dose application, and at every study visit thereafter.

- **Cyclosporine (CsA) whole blood tests**

Analysis of the cyclosporine whole blood levels will be performed locally at the center. Whole blood level for CsA will be assessed by utilizing a monoclonal immunoassay or HPLC-method on blood taken 5 minutes prior to medication intake (C0-h level), as indicated in the visit schedule (C-0h).

- **Certican® (everolimus) whole blood tests**

For the analysis of the everolimus whole blood levels 2 ml of blood should be drawn in EDTA tubes. Analysis will be performed using ELISA method. The C-0h level will be obtained with blood sampling within 5 minutes prior to medication intake.

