### **10.5.6 Pharmacokinetics**

Analysis of the cyclosporine blood levels and Certican® (everolimus) blood levels will be done by treatment group for the treatment phase (up to Month 6) and separately during the follow-up phase.

Blood level values of cyclosporine will be summarized by descriptive statistics by visit and treatment group. The number of patients with deviations from the therapeutic window (see [Section 6.5.2](#)) will be counted and tabulated by visit and in total.

Trough levels of everolimus will be summarized descriptively by visit up to Month 6. The number of patients with deviations from the therapeutic window (see [Section 6.5.1](#)) will be counted and tabulated separately by visit and in total.

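### The Section 6.5.2 cyclosporine table, the key for the deviation counts, scores the Certican arm's pre-switch Visit 3 sample against a target of 0

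*Protocol*

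**What the plan says.** Section 10.5.6 (Pharmacokinetics) refers to Section 6.5.2 for the cyclosporine window and says that the number of patients deviating from it "will be counted and tabulated by visit and in total". The Section 6.5.2 table is therefore the scoring key for a prespecified output as well as dosing guidance.

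The table has four rows:
- Weeks 1–4: 150–200 ng/ml in both arms.
- Weeks 5–6: 100–150 ng/ml in both arms.
- Weeks 7–18: for Certican "Week 7 – Week 18 | 0"; for control 100–150 ng/ml.
- Weeks 18–24: 0 for Certican; 80–120 ng/ml for control.

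The closing sentence of the same subsection says that in the CNI-free group the cyclosporine "dosage will be reduced starting at Week 7 and removed completely the day after".

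On Visit 3 (Baseline visit 2), Section 7 says "This visit may be performed within a time window of week 7 and week 8" and lists the draw for all patients: "Venous blood will be drawn for measurement of the C0-h level of cyclosporine". Section 7.9 adds that for "patients of the CNI-free Certican group cyclosporine blood level will be measured until" the drug is removed, and gives Visit 3, Week 7, as that point. Footnote 5 of Table 7-1 limits drug levels further: "To be assessed only if Sandimmun® Optoral or Certican® are administered at that visit".

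**The concern.** The Visit 3 level is a baseline measurement. It is taken on the day of randomization, when both arms have had the same cyclosporine regimen. A deviation count at that visit should differ between arms only by chance. Under the table as written it differs by construction, because one arm is judged against 100–150 ng/ml and the other against 0. A reader of the by-visit table would see almost universal non-adherence in the Certican arm before that arm had been treated any differently.

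There is a second, lesser point. Week 18 closes one control window and opens the next, and a control sample is scheduled in that week. The deviation count there, and the target an investigator should dose to, depend on which row is read.

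**Working it through.** No sample size, power or alpha figure is involved, so there is no figure of the plan to reproduce. The check maps each scheduled cyclosporine sample to the rows of the Section 6.5.2 table.

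**Inputs**
- Cyclosporine sampling: Visits 2, 3, 5, 6 and 7, that is Weeks 2, 7(–8), 12, 18 and 24 (Table 7-1; Section 7).
- Certican arm: sampled only until cyclosporine is removed (Section 7.9; Table 7-1, footnote 5).
- To be randomized, a patient must be on Sandimmun Optoral (Section 5, inclusion criterion 2 at Baseline visit 2).
- The switch begins the day after randomization. Both Day 1 doses still contain cyclosporine, and the first dose without it is on Day 2 (Sections 4 and 6.5.1).
- Planned numbers: 162 Certican and 82 control (Section 10.7).

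**Scheduled samples per table row**

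| Row | Certican target (ng/ml) | Certican samples | Control target (ng/ml) | Control samples |
|---|---|---|---|---|
| Weeks 1–4 | 150–200 | Visit 2 | 150–200 | Visit 2 |
| Weeks 5–6 | 100–150 | none | 100–150 | none |
| Weeks 7–18 | 0 | Visit 3 | 100–150 | Visits 3, 5, 6 |
| Weeks 18–24 | 0 | none | 80–120 | Visits 6, 7 |

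**Visit 3.** The Certican sample is drawn on drug, before the switch, and falls in the row with target 0. Unless cyclosporine is re-added later, it is the only scheduled Certican sample that the 0 can meet (1 of 1 in that row). The row that would suit it, Weeks 5–6, meets no scheduled sample. At 125 ng/ml a Certican patient is a deviation and a control patient is in range. The ceiling is 162 of 162 planned Certican patients, before drop-out. Against 100–150 ng/ml only those outside that range would count.

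**What the other text says about the same sample**
- Last sentence of the Sandimmun Optoral subsection: cyclosporine is still being given at the start of Week 7, so 0 cannot be its target then.
- Table 4-1, footnote 1: 100–150 ng/ml for Weeks 5–18, with no split by arm.
- Section 6.5.1: 100–150 ng/ml for Weeks 7–18 in control patients only. This leaves the Certican Visit 3 sample with no target, which is not the same as 0.

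**Week 18.** The shared endpoint appears in Table 4-1, Section 6.5.1 and Section 6.5.2.
- Both windows accept 100–120: a width of 120 − 100 = 20 ng/ml.
- At least one accepts 80–150: a width of 150 − 80 = 70 ng/ml.
- They disagree on 80 to <100 and on >120 to 150: (100 − 80) + (150 − 120) = 50 of those 70 ng/ml.

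This is a span of levels and not a share of patients. The documents give no trough distribution, so any share needs an assumption. Take a normal Week 18 trough X with mean 90–125 and SD 20–40 ng/ml. The share whose status depends on the row is P(80 ≤ X < 100) + P(120 < X ≤ 150). At mean 110 and SD 30 this is 0.211 + 0.278 = 0.489, about 40 of 82. Over the whole assumed range it runs from 36% to 59%, about 29 to 48 of 82.

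**The case against.** The best reply is that nobody would score the table this way. The protocol makes its intention plain: patients are on cyclosporine at randomization, the switch starts the next day, and the sentence directly below the table says so. A 0 is not a therapeutic window but a marker that the drug has been withdrawn. Assigning samples to rows and defining the overall total is normally the analysis plan's task, and that plan is not shown. A dosing table also need not have a visit in every row.

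Much of this stands. The intention is clear, the 162 is a ceiling under the literal reading and not a forecast, and the empty Weeks 5–6 row is not itself an error. It does not remove the point, because Section 10.5.6 names this table as its key. A programmer who follows the reference gets a wrong Visit 3 count, and one who gets it right has departed from the cited rule. That is a wrong entry, which differs from detail left for later.

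On Week 18 the reply is stronger. A shared endpoint is a common way to mark a change of target. The trough is drawn before the dose and so reflects the interval just ended. Section 6.5.2 asks for its recommendations to be followed only so far as clinically feasible. An analyst could settle this sensibly, which is why it is secondary.

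A reader might also infer that the 0 should simply be deleted. The documents do not support that. Section 6.5.2 (Certican, step 4) allows cyclosporine to be added back in the Certican arm, and footnote 5 of Table 7-1 then calls for a level at those visits. There the 0 does useful work, because it flags re-exposure.

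**Conclusion.** The point holds and is minor. As written, the table gives a wrong Certican deviation count at Visit 3 and an arm difference where the regimens are identical. It also conflicts with the end of its own subsection and with Table 4-1, footnote 1. The Week 18 overlap is a genuine but lesser ambiguity in three places. The two issues concern different arms and visits and should not be added together.

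The conclusion assumes that the Section 6.5.2 table is applied literally, as Section 10.5.6 directs. The patient counts are planned numbers, and the Week 18 percentages rest on an assumed distribution.

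Three stronger readings are not supported:
- That the error biases the efficacy comparison. The affected output is descriptive, and the primary GFR analysis does not use trough deviations.
- That it alters the per-protocol set. The open list of exclusion reasons in Section 10.1 does not name trough-window deviations.
- That it contaminates the overall total. Section 10.5.6 does not define that total, and the Visit 3 error would carry into it only if it means patients who ever deviated.

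**What to change.** In Section 6.5.2, state that 100–150 ng/ml applies in both arms up to and including the pre-switch Visit 3 sample, whether that falls in Week 7 or Week 8. State that the Certican target of 0 applies only after cyclosporine has been removed. Keep the 0 from then on, so that re-added cyclosporine is still counted. Bring the control-only restriction in Section 6.5.1 into line.

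As a secondary correction, make the control windows disjoint at Week 18 in Table 4-1, Section 6.5.1 and Section 6.5.2. One option is 100–150 ng/ml up to and including the Week 18 sample and 80–120 ng/ml afterwards. The clinical team should confirm the boundary, since it is also a dosing target. Name the week as well as the visit: Tables 4-1 and 7-1 put Visit 6 at Week 18, but Sections 6.5.5 and 10 use that label for Month 6.

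Every scheduled sample then falls in exactly one window. The cost is a few lines of wording, with no new samples and no change to sample size or power.
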